## Abstract

**Background:**

Severe weight loss through means of bariatric surgery has been associated with loss of muscle mass due to lack of absorption of protein. The aim of this RCT is to investigate the effectiveness of protein supplementation in reducing the risk of developing protein malnutrition and muscle wasting in post-bariatric surgery patients in Qatar.

**Methods and analysis:**

The study was based at the Department of bariatric and metabolic surgery, Doha metropolitan and regional areas. It is envisaged that approximately 160 post-bariatric surgery patients will be randomized and followed up for 6 months. These will be males and females obese (BMI >35) Qatari patients between the aged 18–60 years. Subjects with renal or liver disease and those with past history of bariatric surgery will be excluded. By the completion of the trial, patients who took less than 80% of the supplement will be further excluded from the final analysis. Protein supplement (Cubitan,Protein, Nutricia, Netherlands) that contain daily intake of 20 g of protein to be taken orally 3 times a day throughout the study period. The placebo group will receive identical ampule containing zero-protein with exact instructions as per the intervention group. Body weight, muscle and fat mass, total protein, albumin, vit B12, Magnesium and Zinc will be measured at baseline and every follow up/study visit. Study variables will be compared between the 2 groups at different stages of the trial, including baseline, using Sample T-test (paired and unpaired) and the significance level will be confirmed with the 95% confidence interval with alpha error set to 0.05.

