**Strengths and limitations of this study:**

One major strength of our study is that our population is a distinctive population (Qatari Obese patients) where results from international studies may not apply to the local and unique context. A local study like ours will provide healthcare providers in Qatar an opportunity to ensure good clinical practice and healthy and sustainable weight loss following bariatric surgery.

The well-designed double-blinded RCT will almost certainly provide us with the evidence-based clinical practice guideline that we seek as health professionals.

One limitation of our study is the slight discrepancy in caloric content of the intervention and the placebo (250 cal and 100 cal, respectively). However, it is the intervention that has the higher caloric content, in which case it may not influence the results in the direction of our hypothesis that protein supplementation leads to lower fat mass and higher muscle mass.

Another limitation is that the use of the intervention and the placebo are not objectively measured. However, all efforts will be made to ensure compliance and reporting of consumption of products.

A third limitation could be loss to follow up. Participants may cease to participate, particularly, once they have lost “sufficient’ weight and gained the fitness to consume any type of foods they desire. This is common in late stages of post-bariatric surgery (beyond 3 months). We feel that this may be a challenge, particularly in reference to our specific population. However, such findings albeit negative, should serve in improving the clinical practice delivered by healthcare providers.

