## Methods and design

This study is a double-blinded randomized control trial where both investigators and participants will be blinded to the treatment (intervention and placebo products are identical and unlabeled). The researchers will recruit participants early 2017. The randomization will be done on a weekly basis within blocks of 8 or 10 patients. This is roughly the number of patients available per week. A simple randomization process will be employed to assign patients to either groups- intervention & placebo. Using a computer generated random list, the treatment and the placebo will be allocated in a random manner to numbers that label individual patients. For the blinding, a dietician will assign the treatment and the control to patients as per the randomization results.

Both the intervention and control groups will receive standard dietary instructions in post-bariatric surgery period including hospital stay (1–2 days) and every month thereafter. The intervention group will receive protein supplement and the placebo group zero-protein supplement everyday over the study period (6 months). The placebo & the protein supplement slightly differ in the caloric content (the difference is 150 kcal/bottle). Although this difference is not clinically significant, particularly for the early post-operative phase, this issue will be addressed as a limitation for this study.

Investigators and researchers, including providers of care (rehab staff) in this study will be blinded to the intervention, i.e. they will not be aware of who is on protein supplement and who is on placebo. Patients will also be blinded to the intervention, i.e. they will not be aware whether they are taking protein or zero protein supplement. This dietitian is also responsible for filling the intervention & control ready-to-feed shakes into identical bottles labeled either A or B. The dietician will not have any other responsibility such as data entry or follow up of participants, as this will be done by the PI and research team. Un-blinding will be unlikely within the settings of our trial, however, any suspicion of un-blinding will be dealt with appropriately and may result into the cessation of participation in the trial.

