### Exclusion criteria

Patients will be excluded from participating in the trial if they have the following criteria:Any Renal or liver disease because that may affect protein or albumin level in body.Past history of bariatric surgery (Gastric Band & Gastric bypass)Patients will be further excluded after starting the trial if they did not take at least 80% (minimum 24 bottles per month) of their allocated intervention or placebo products throughout the trial.

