#### Study visits

Patients follow up visit once every month post-surgery at the Bariatric Dietician Clinic in OPD department at HGH, and covers the following:A.Post-surgery dietary advice, to sustain a hypo caloric and protein-rich diet.B.Anthropometric parameters for body composition (see below).C.All patients will be followed up through weekly phone calls to ensure compliance and adherence to the study protocol. Questions such as “how many bottles of supplements are left?” Or, “how many bottles have you had so far?” will be asked. Patients will be asked to use a diary to register their daily use of the products as well as fill the forms provided by the hospital in relation to consumption of supplement.D.Collection of blood sample will take place following an overnight fasting. All blood markers will be measured and calculated in the central laboratory at HGH.

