## Statistical analysis

Data analyses will be performed using the statistical software SPSS package 23. The main aim is to analyze Body composition and other anthropometric changes throughout the follow up. The normality of the variables will be assessed by the Kolmogorov-Smirnov test. Non-parametric tests will be used in case of non-normal distributions of variables. Characteristics and demographics of participants will be summarized, based on the assignment of treatment or placebo, using means and standard deviations (SD) for quantitative variables. Baseline data for the two groups will be compared using two tailed independent samples t-tests and the *P* value of this difference for each variable will be provided. During the follow-up, changes in weight, body fat percentage, muscle mass, total protein level, albumin level, vit B12, Zinc and Magnesium will be compared within groups using paired t-test and between groups using independent sample t-test. In the case of non-normal distribution of variables, any two independent (unpaired) samples Student’s t test will be replaced by Mann-Whitney U test. However, in the case of Two dependent (paired) samples Student’s t test, Wilcoxon signed rank (paired samples) test will be used. A multiple linear regression model will also be conducted to adjust for age and gender will be conducted. Other fundamental confounders such as diet intake are not incorporated into the multiple binary regression model. This is primarily because post-bariatric patients within the 1st few months (early post-operative phase) are both unable and not allowed to take any solid foods and few specific liquid foods such as milk and soups are recommended to them by the dietician. All patients are trained to follow such diet. Moreover, being an RCT, it is expected that all confounders (including hidden confounders) are balanced between the 2 groups and no assessment of baseline variables such as diet, physical activity and any other biological differences between the 2 groups is required. This is consistent with the CONSORT statement for RCTs.

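### The only final analysis the article describes leaves out randomised patients who took less than 80% of the product by self-report, so the groups compared are not the randomised groups

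*Protocol article*

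**What the plan says.** The Abstract (Methods and analysis) says that "patients who took less than 80% of the supplement will be further excluded from the final analysis". The Exclusion criteria list the same rule as one that operates once the trial is under way: "Patients will be further excluded after starting the trial if they did not take at least 80% (minimum 24 bottles per month", applied to active product and placebo alike.

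On how intake is known, Study visits describes weekly phone questions about bottles used or left, hospital forms, and a diary: "Patients will be asked to use a diary to register their daily use of the products". Strengths and limitations concedes that "the use of the intervention and the placebo are not objectively measured".

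Statistical analysis compares changes "between groups using independent sample t-test" (Mann-Whitney if non-normal) and names no analysis set. It justifies leaving diet out of the regression model partly because "it is expected that all confounders (including hidden confounders) are balanced between the 2 groups". Sample size raises 130 to 160 to allow for dropout, non-compliance and loss to follow-up.

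Methods and design adds, separately, that "any suspicion of un-blinding will be dealt with appropriately and may result into the cessation of participation in the trial".

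**The concern.** Randomisation makes the two arms comparable as allocated. It gives no such assurance for subsets chosen by what patients do later. A patient who keeps taking a 250 kcal product with 20 g of protein need not resemble one who keeps taking a 100 kcal, protein-free, fat-free product. If adherence is related to change in fat or muscle mass and the proportion kept differs between arms, the comparison shifts even when the supplement does nothing. The shift can go either way. If better adherers lose more fat, the arm with lower adherence is the more strongly selected and appears to do better. If patients who lose weight fast take less product, the sign reverses.

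Because intake is self-reported, misreporting also helps decide who is analysed. The damage may be permanent: if excluded patients are no longer measured, no later analysis can put them back.

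**Working it through.** **1. What the plan allows for.** From Sample size: 130 required, 160 planned. 160 − 130 = 30, and 30/160 = 18.75%, inside the stated 15% to 20%. Check: 130/(1 − 0.1875) = 160. So the plan provides for losing about 30 randomised patients to all causes together, non-compliance among them. The 80% threshold agrees with its own bottle count: 24/30 = 0.80.

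**2. Reference difference.** From the cited means, fat-mass change is 78.2 − 59.9 = 18.3 kg (intervention) and 68.2 − 53.9 = 14.3 kg (placebo), a difference of 4.0 kg. The article does not say that this contrast drove the sample size.

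**3. Spurious difference with no true effect.** Treat adherence as a normal score with correlation r to the outcome, and keep the top fraction p of an arm. The mean outcome in those kept shifts by SD × r × φ(c)/p, where c is the cut-off that leaves fraction p. The bias is the difference between arms.

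Assumed, not in the document: SD of fat-mass change 7 to 10 kg, r = 0.3 to 0.5, and the split of exclusions by arm. Overall exclusion is held at 18.75%.

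| Adherence by arm | φ(c)/p in each arm | Difference | × 7 × 0.3 | × 10 × 0.5 |
|---|---|---|---|---|
| 81.25% v 81.25% | equal | 0 | 0 | 0 |
| 77.5% v 85% | 0.387 v 0.274 | 0.113 | 0.24 kg | 0.56 kg |
| 72.5% v 90% | 0.460 v 0.195 | 0.265 | 0.56 kg | 1.33 kg |

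**4. Type I error.** Simulation of 80 per arm, no true effect, 20,000 runs, r = 0.3 to 0.5, nominal 5%:

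| Excluded by arm | Type I error |
|---|---|
| 18.75% v 18.75% | about 5% |
| 15% v 22.5% | 5.5% to 6.3% |
| 10% v 27.5% | 7% to 12% |
| 5% v 32.5% | 11% to 24% |

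**5. Power if everyone is analysed.** The stated 65 per group cannot be reproduced from the listed means and SDs. For example, fat mass at follow-up (6.0 kg; SDs 15 and 11.5) needs 105 per group at 90% power, two-sided 5%. The standardised effect that 65 per group implies is therefore used: (1.960 + 1.282) × √(2/65) = 0.569 SD. With 80 per group, power is Φ(0.569 × k × √40 − 1.960), where k is the share of the active arm that benefits:

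| Active arm gaining nothing | k | Power, 160 analysed | Analysed total for 90% (2 × 65/k², rounded up per group) |
|---|---|---|---|
| 0% | 1 | 94.9% | 130 |
| 15% | 0.85 | 86% | 180 |
| 18.75% | 0.8125 | 83% | 198 |
| 20% | 0.80 | 82% | 204 |

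**The case against.** The adherent-set analysis looks deliberate. The primary objective speaks of participants who received supplement or placebo, and the sample size is inflated for non-compliance. The effect in people who take the product is a legitimate question. That weakens any charge that the trial answers the wrong question, but it does not restore comparability: an effect in adherers cannot be read off by comparing self-selected adherers in each arm.

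The bias may also be small. Equal exclusion by the same mechanism produces none under the null, and a modest imbalance produces little. This stands, and it limits the size of the claim. Nothing in the plan secures equal exclusion, however.

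Three stronger readings are tempting, and the document does not support them:

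- *Patients suspected of un-blinding are removed from the analysis.* Methods and design calls un-blinding unlikely and says only that participation may end. It is silent on the data.
- *The article itself says that adherence depends on weight loss.* The relevant sentence, "Participants may cease to participate, particularly, once they have lost" enough weight, concerns loss to follow-up and is worded as a possibility. A similar link for product intake is plausible but not stated. Patients who leave altogether have no six-month outcome in any analysis set, so dropping the 80% rule does not solve that problem.
- *No analysis of all randomised patients exists.* A separate analysis plan is not shown. What can be said is that the article describes none, and that the one it does describe excludes non-adherers. An analysis plan that made all randomised patients primary would contradict the published wording.

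**Conclusion.** The rule is wrong as written and must be changed. It is an affirmative instruction, given twice, to define the final analysis by self-reported behaviour after randomisation, and it conflicts with the reliance on randomisation in Statistical analysis.

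Within the plan's own allowance for losses, the illustrated bias in fat-mass change runs from zero with equal exclusion to about 1.3 kg with 72.5% v 90% adherence. At that upper end it is about a third of the 4.0 kg derivable difference (1.33/4.0 = 0.33), with type I error of 7% to 12%. These figures rest on the assumed SD, correlation and split by arm. A more uneven split would give more and a more even one less. That the protection of randomisation is lost does not depend on those assumptions.

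**What to change.** - Delete the 80% rule from the Exclusion criteria and from the final-analysis definition in the Abstract.
- State that the primary analysis includes all randomised patients in their assigned arm, whatever their adherence.
- Keep measuring patients who stop the product at the scheduled visits.
- Keep the 80%-adherent set as a labelled supplementary per-protocol analysis.
- State that patients whose participation ends on suspected un-blinding stay in follow-up and in the primary analysis as far as consent allows.

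**Cost.** The changes are to wording, plus attendance at visits already scheduled; the article describes the measurements as routine practice. The real price is dilution by non-adherence. The stated 90% power should be restated for this analysis set: about 82% to 86% with all 160 analysed if 15% to 20% of the active arm gain nothing, and 90% would need about 180 to 204 analysed patients. Both figures rest on the effect size implied by 65 per group, so the basis of that number should be given at the same time.

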**Ethics and dissemination:**

Protein supplementation for post-bariatric patients is not yet a standard procedure at Hamad Medical Corporation in Qatar and requires an RCT to establish evidence-based clinical practice guidelines. This study was approved by the Hamad Medical Corporation IRB and MRC committees (approval no. 16433/16).

**Trial registration:**

ClinicalTrials.gov NCT03147456 (registration date: 18 April 2017).

**Strengths and limitations of this study:**

One major strength of our study is that our population is a distinctive population (Qatari Obese patients) where results from international studies may not apply to the local and unique context. A local study like ours will provide healthcare providers in Qatar an opportunity to ensure good clinical practice and healthy and sustainable weight loss following bariatric surgery.

The well-designed double-blinded RCT will almost certainly provide us with the evidence-based clinical practice guideline that we seek as health professionals.

One limitation of our study is the slight discrepancy in caloric content of the intervention and the placebo (250 cal and 100 cal, respectively). However, it is the intervention that has the higher caloric content, in which case it may not influence the results in the direction of our hypothesis that protein supplementation leads to lower fat mass and higher muscle mass.

Another limitation is that the use of the intervention and the placebo are not objectively measured. However, all efforts will be made to ensure compliance and reporting of consumption of products.

A third limitation could be loss to follow up. Participants may cease to participate, particularly, once they have lost “sufficient’ weight and gained the fitness to consume any type of foods they desire. This is common in late stages of post-bariatric surgery (beyond 3 months). We feel that this may be a challenge, particularly in reference to our specific population. However, such findings albeit negative, should serve in improving the clinical practice delivered by healthcare providers.

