#### Measurements

Baseline measurement of body composition (fat mass and muscle mass), height and weight will be conducted on day one of the trial, using Tanita body composition instrument and other physical body measures.Baseline blood test for total protein, albumin, Vit B12, Zinc and Magnesium levels will be collected.All of the above measurements will be repeated at 1 month, 3 months and at the end of the follow up period (6 month).

*Note: All of the above measurements and the collection of blood sample is routine practice for post-bariatric surgery patient.

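### Leaving is expected to follow weight lost after month 3, yet the tests and the 80% intake rule drop those who leave; this can bias the 6-month comparison

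*Protocol article*

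**What the plan says.** Under Strengths and limitations, the protocol article names loss to follow-up as a possible problem: "Participants may cease to participate, particularly, once they have lost" enough weight and can again eat what they like. On timing it says: "This is common in late stages of post-bariatric surgery (beyond 3 months". No analytic response follows there.

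The Measurements section provides the data that a response would need: "All of the above measurements will be repeated at 1 month, 3 months" and at 6 months. The Statistical analysis section compares changes within groups by paired t-test and "between groups using independent sample t-test", with Wilcoxon or Mann-Whitney tests if distributions are not normal. It adds: "A multiple linear regression model will also be conducted to adjust for age and gender". The abstract places the comparisons at separate time points: "Study variables will be compared between the 2 groups at different stages of the trial".

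The abstract also fixes who is analysed: "patients who took less than 80% of the supplement will be further excluded from the final analysis". The Exclusion criteria repeat this as 24 bottles a month throughout the trial. The Sample size section adds 15% to 20% for dropout, non-compliance and loss, going from 130 to 160.

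**The concern.** The authors expect some patients to leave because of how much weight they have lost. Percentage weight reduction is a secondary outcome and is closely tied to the primary one, change in fat and muscle mass. A two-sample test on 6-month change uses only patients who have a 6-month value. It ignores what was already known at months 1 and 3 about those who left, and adjusting for age and gender does not bring that back.

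If one arm loses weight faster, more of its large responders can go missing, and the completers' fat difference then understates the effect. Muscle can move the other way: large weight losers tend to have lost more muscle, so their exit can flatter the arm they leave. Extra recruitment protects power but does nothing about selective loss. The Statistical analysis section relies on randomisation to balance confounders, but that covers the groups as randomised and not the groups left after selective exit.

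**Working it through.** **1. Does the intake rule remove these patients?** 80% of 6 months is 0.80 × 6 = 4.8 months of product. A patient who takes every bottle and stops at month 3 reaches 3/6 = 50%. Such a patient leaves the final analysis whichever test is used, even if a 6-month measurement exists.

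**2. What does the allowance cover?** 160 enrolled to 130 evaluable is 30/160 = 18.75% loss. Dividing 130 by (1 − 0.20) gives 163, close to 160. The allowance is about numbers only.

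**3. How large could the bias in fat be?** The document gives no dropout model, so this is an illustration.

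- From the Sample size section: fat loss is 78.2 − 59.9 = 18.3 kg on intervention and 68.2 − 53.9 = 14.3 kg on placebo, a difference of 4.0 kg. This is used as the true 6-month difference.
- Assumed: 3-month difference 2.8 kg; SD 6 kg at month 3 and 7 kg at month 6; correlation r of 0.85 or 0.5 between them.
- Assumed: the same leaving rule in both arms, P(leave) = 1/(1 + exp(−(x − c)/s)), where x is month-3 fat loss relative to the control mean. Lighter loss has c = 10, s = 3; heavier loss has c = 6, s = 2.

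| Scenario | r | Loss, intervention v control | Completers' difference |
|---|---|---|---|
| Lighter | 0.85 | 18.3% v 10.5% | 3.45 kg |
| Heavier | 0.85 | 32.3% v 19.5% | 3.03 kg |
| Lighter | 0.5 | as above | 3.67 kg |
| Heavier | 0.5 | as above | 3.43 kg |

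The attenuation runs from (4.0 − 3.67)/4.0 = 8% to (4.0 − 3.03)/4.0 = 24%. Average loss is (18.3 + 10.5)/2 = 14.4% in the lighter case, inside the plan's allowance. It is (32.3 + 19.5)/2 = 25.9% in the heavier case, outside it.

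**4. Is there bias without an effect?** With no product effect and the same leaving rule in both arms, the completers' difference is zero within simulation error.

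**5. What about muscle, and arm-specific leaving?** A second set of assumptions works in SD units: 19% control loss, and month-3 weight loss correlated 0.8 with 6-month fat and 0.5 with muscle.

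- Same leaving rule, weight loss differing between arms: a fat effect of −0.57 becomes −0.51 or −0.45 (log-odds slope 1 or 2), and a muscle effect of 0.30 becomes 0.32 to 0.38.
- No true effect, leaving rule differing by arm: spurious differences of 0.13 to 0.29 SD in fat and 0.08 to 0.18 SD in muscle.

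**6. How far do the earlier visits repair it?** With the inputs of step 3 and r = 0.85:

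- Leaving depends on month-3 loss only: predicting month 6 from month 3 returns 4.0 kg.
- Leaving depends on the average of months 3 and 6: it returns about 3.8 kg (lighter) and 3.6 kg (heavier).
- Leaving depends on month 6: it returns about 3.6 and 3.2 kg.

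In the last two cases completers alone give about 2.4 to 3.2 kg.

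**The case against.** A reader might infer that these tests are valid only when dropout is unrelated to outcome, so that the 6-month comparison is certain to be biased. The document does not support that. For a difference between arms, step 4 shows no bias when both arms leave by the same rule and the product does not affect weight loss. The wording is also cautious: patients may leave, and regained ability to eat is named beside weight. So the claim is that the analysis can bias the result.

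A reader might also infer that a mixed model fully repairs the estimate. It does so only if leaving depends on values already recorded. The authors place leaving beyond month 3, so weight lost after that visit may matter, and step 6 shows partial recovery in that case. The Study visits section lists anthropometry at monthly visits; if body composition is recorded then, the gap narrows.

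The size is modest against sampling error. At 65 per arm with SD 7, the standard error is 7 × √(2/65) = 1.23 kg, so a bias of 0.33 to 0.97 kg is about 0.3 to 0.8 of a standard error. This stands, but a bias of this kind does not shrink as the trial grows.

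Finally, missing-data handling is often left to an analysis plan, and no sentence rules out imputation. But the article itself names the tests and fixes the exclusion from the final analysis. Those are stated choices, not omitted detail. Body measurements are described as routine, so stopping the product need not mean a missing 6-month value; the 80% rule discards that value all the same.

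**Conclusion.** The concern holds as a risk. The plan anticipates exit related to outcome, then fixes tests that ignore the earlier values of those who leave and an analysis set that removes them by rule. Bias in the 6-month difference needs either a product effect on weight loss or leaving rules that differ by arm. Neither can be safely excluded: the article hypothesises lower fat and higher muscle mass, makes weight reduction an outcome, and uses products that differ by 150 kcal per bottle. The within-group paired comparisons are open to selection even without an arm difference.

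The figure of 3.0 to 3.7 kg against a true 4.0 kg rests on the assumed SDs, correlations and month-3 leaving rule, and only the 4.0 kg comes from the document. Other leaving rules give other sizes, and arm-specific leaving can create a difference where none exists. This should be changed before analysis, but it does not show that the result will be wrong in a known direction.

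**What to change.** Make the primary analysis a mixed model for repeated measures, one for fat mass and one for muscle mass, on all randomised patients with any post-baseline value, regardless of the 80% intake rule. Include arm, visit (1, 3 and 6 months), arm-by-visit, baseline and baseline-by-visit, with unstructured covariance, and read the treatment effect at 6 months. SPSS 23, the named software, can fit it. State that patients who stop the product are still measured at the planned visits where they agree.

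Keep the 80%-intake set as a supportive per-protocol analysis. Changing the model while leaving the exclusion in place would not help, because the same patients would still be absent.

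Add one sensitivity analysis: impute the missing 6-month values from arm and earlier weight, fat and muscle, then shift them over a stated range. Earlier weight belongs in the imputation because leaving is expected to follow weight, which a model of muscle alone does not see. The shift covers leaving driven by weight lost after the last visit.

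The cost is a little more analysis work, and the 80%-intake result is no longer primary. No new visits, patients or measurements are needed. The model relies on data missing at random given the recorded values, which is a weaker condition than the completer comparison needs.
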